#### Secondary/additional outcomes

Additional assessments will include evaluation of depressive symptoms using the PHQ-9, a widely used and validated self-rated depression scale [23]. Functional health status will be assessed using the 36-Item Short Form Survey (SF-36), a multi-purpose, short-form health survey that yields two psychometrically based components: a physical component summary and a mental component summary, which has proven useful for comparing the relative burden of diseases [24]. Epilepsy control will be assessed via self-reported seizure frequency. Quality of life will be assessed with the Quality of Life in Epilepsy (QOLIE-31) self-administered questionnaire which comprises 7 components including seizure worry, overall quality of life, emotional well-being, energy-fatigue, cognitive functioning, medication effect, and social function [25, 26]. These domains (score on PHQ-9, score on SF-36, self-reported seizure frequency, and score on QOLIE-31) will be assessed for differences between the two groups looking at mean and median values at baseline and 13 and 24 weeks of trial and change over time from baseline to 24 weeks of trial. A type I error rate of 0.05 will be considered significant.

Other factors assessed in the trial include epilepsy self-management competency, self-efficacy, social support, and stigma. Self-efficacy will be measured with an Epilepsy Self-Efficacy Scale (ESES) 2000 version. The ESES was developed based on Bandura’s conceptualization of self-efficacy to assess a person’s confidence in his or her ability to use self-management strategies. Previous studies show acceptable construct validity and high test-retest reliability in the ESES [27–29]. Social support will be measured with the Multidimensional Scale of Perceived Social Support (MSPSS), a 12-item scale that measures an individual’s perception of social support provided by family and friends, as well as satisfaction with that support [30]. Stigma for epilepsy will be measured using the 24-item Stigma Scale of Epilepsy (SSE) developed by the Demonstration Project on Epilepsy as part of the WHO/ILAE/IBE Global Campaign against Epilepsy [31, 32]. The SSE is a validated, versatile, and sensitive instrument which has been used mainly in resource-poor settings to study stigma in epilepsy.

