### Data analysis

Descriptive analyses will compare the individuals assigned to SMART or WL using Student’s *T*-test, Fisher’s exact test, and non-parametric tests when appropriate. The primary outcome is whether there is a difference in the proportion of individuals with reductions in the total number of NHEs in the prior 6 months, at baseline, and at follow-up (6 months after randomization) between SMART and WL, compared using a Fisher’s exact test. We will also test for the difference in NHE counts between baseline and follow-up using a non-parametric Wilcoxon-Mann-Whitney test (the distribution of this measure is expected to be non-normal based on our prior experience). Exploratory longitudinal mixed models with a subject-level random effect will be conducted to investigate a binary variable of no NHEs versus at least one NHE and for a count measure of total NHEs from baseline to 10 and 24 weeks. Explanatory variables will include study site, age, gender, race/ethnicity, number of seizure medications, rural/urban continuum status, and attendance or deviations from the study protocol. Analysis will be performed for the intention-to-treat population (all participants enrolled to receive the SMART trial), for the safety population (all participants who received any portion of the SMART intervention), and for the per-protocol population (all participants who completed the SMART intervention). There will be a delay between randomization and baseline assessments for individuals enrolled for both the SMART trial and the waitlist, which may vary based on the recruitment time required for cohorts and the number of cohorts that can be accommodated at one time. Every effort will be made to insure steady recruitment and sufficient numbers of cohorts to accommodate those recruited. In addition, the specific cohorts will be able to be identified for analysis, and if we find marked variability between the cohorts or the delay in starting the intervention, this will be addressed by the data monitoring committee.

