The 12-month and 18-month measurements of NHEs will be compared to baseline and 6-month measurements as well. We will also examine change-over-time in the secondary outcomes using parametric and/or non-parametric tests as deemed appropriate for each measure. NHE measurements will reflect the preceding 6-month time period, except for the 13-week time period. The 13-week NHE measurement will reflect the time period following baseline (when individuals participating in SMART will be having their “intensive” group sessions), and it will be used to assess for within-subject differences from baseline to 13-week and 13-week to 6-month time periods. Note that the 13-week to 6-month NHE count will be derived by subtracting the measurement taken at 13 weeks from the one taken at 6 months. This will allow for a greater understanding of the time course for when the expected reductions occur in the SMART group, which we expect to mostly occur after the “intensive” 8 group sessions have ended. A secondary analysis of NHEs will include a comparison of hospital and emergency department visits. A 2-sided type I error rate of 5% will be considered significant.

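### PHQ-9, SF-36 and QOLIE-31 each get two 24-week comparisons at 0.05 (score and change from baseline); neither is named as the result, and no baseline-adjusted analysis is named

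*Protocol article*

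**What the plan says.** The Secondary/additional outcomes section lists the PHQ-9, SF-36 and QOLIE-31 scores, together with self-reported seizure frequency. It says that these "will be assessed for differences between the two groups looking at mean and median values at baseline and 13 and 24 weeks of trial and" also on "change over time from baseline to 24 weeks of trial". The next sentence sets the level: "A type I error rate of 0.05 will be considered significant". The Data analysis section makes it two-sided.

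On method, the Data analysis section says only: "We will also examine change-over-time in the secondary outcomes using parametric and/or non-parametric tests as deemed appropriate for each measure". The models with covariates in that section are exploratory and concern negative health events (one binary variable, one count). The covariate list follows them: "Explanatory variables will include study site, age, gender, race/ethnicity, number of seizure medications, rural/urban continuum status", and then attendance or protocol deviations. A scale's own baseline score is not in it.

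The Outcomes and analysis section schedules a baseline assessment in both arms. The Data analysis section adds that baseline comes after randomization, with a delay that may vary with cohort recruitment. The Phase 2 section says that participants are not blinded.

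**The concern.** The 24-week score difference and the difference in change are two estimates of one treatment effect. They differ only in how they treat baseline: the score ignores it and the change subtracts it in full. If the arms differ at baseline by chance, one estimate moves up and the other down. Nothing in the article says which one answers the question, so significance on either could be reported as an effect on that scale.

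The Background section hypothesizes that SMART improves quality of life, functioning, and physical and mental health, and these scales are how that would be judged. Two rival tests loosen the standard of evidence for each scale. At the same time they use the baseline data less efficiently than a single adjusted comparison would.

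**Working it through.** **Inputs from the article.** Sample size 160, 1:1, with 20% attrition: 160 × 0.80 = 128, or 64 per arm. This reproduces the article's analysed number. The powers of 86% and 89% in Sample size calculations belong to the two primary outcomes; none is given for the scales.

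**Assumptions.** Equal SDs at baseline and 24 weeks; correlation ρ between them of 0.3 to 0.7 (the article gives none); an illustrative effect of 0.5 SD; approximate normality; a baseline unaffected by allocation; clustering of SMART participants in groups ignored.

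**Precision.** The variance per participant, in SD² units, is 1 for the score, 2(1 − ρ) for the change and 1 − ρ² for the adjusted score. With n = 64 per arm, the noncentrality of the two-sided t-test is 0.5 × √(64/2) / √variance = 2.83 / √variance.

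| ρ | Variance: score / change / adjusted | Power: score / change / adjusted |
|---|---|---|
| 0.3 | 1 / 1.40 / 0.91 | 80.1% / 66.0% / 83.7% |
| 0.5 | 1 / 1.00 / 0.75 | 80.1% / 80.1% / 90.0% |
| 0.7 | 1 / 0.60 / 0.51 | 80.1% / 95.2% / 97.6% |

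The better planned test has variance min(1, 2(1 − ρ)). Its ratio to 1 − ρ² is 1.10 at ρ = 0.3, 1.33 at 0.5 and 1.18 at 0.7, and it peaks at 0.5. The power gain over that test is 83.7 − 80.1 = 3.6 points, 90.0 − 80.1 = 9.9 points and 97.6 − 95.2 = 2.4 points.

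**Two tests of one effect.** With no effect, the score and change statistics have correlation √((1 − ρ)/2), which is 0.592, 0.500 and 0.387 at ρ = 0.3, 0.5 and 0.7. From the bivariate normal distribution, the chance that at least one is significant at two-sided 0.05 is 8.8%, 9.1% and 9.4%. Independent tests would give 1 − 0.95² = 9.75%. Adding the listed 13-week comparison, with equal correlations between visits, gives about 13%.

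**Disagreement.** With a true effect of 0.4 SD and ρ = 0.5, 400,000 simulated trials gave one significant and one non-significant test in about 32%.

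**Effect of a chance baseline imbalance.** One standard error is √(2/64) = 0.18 SD. At ρ = 0.5 the score estimate shifts by 0.5 × 0.18 = +0.09 SD and the change estimate by (0.5 − 1) × 0.18 = −0.09 SD.

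**Effect of a baseline shift caused by allocation.** Suppose that knowing the allocation moves one arm's baseline by b SD and that this has gone by 24 weeks. The score is unaffected, the adjusted estimate moves by ρb in size (0.5b at ρ = 0.5), and the change moves by the full b.

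**The case against.** The strongest objection concerns the baseline. A reader might infer that any baseline difference between randomized arms is chance, so that the baseline comparison can be dropped and adjustment is automatically safe. The article does not support this. Baseline follows randomization after a varying delay, in unblinded participants, so these self-reports may be completed by people who already know they are on the waitlist. The baseline comparison then has diagnostic value, and the variance formulas describe an ideal case. This stands, and it shapes the fix. It does not rescue the plan, because the planned change score leans on the same baseline more heavily than an adjusted model does.

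Second, the article names no test for these scales and leaves the choice open. An adjusted model is parametric and not excluded, and a full analysis plan may specify one. So it would be wrong to say that the article rules adjustment out. It does, however, state the score comparison, the change comparison and the 0.05 level, and the concern is with that stated pair.

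Third, 0.05 reads as a per-test level for secondary outcomes, and no family-wise control is claimed for them. A reader might set 9% against 5% as a broken promise; it is not one.

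Fourth, leading with a rise in power from 80% to 90% would overstate the benefit, since ρ = 0.5 is the most favourable case. Finally, the two answers may conflict but need not: in the 0.4 SD example they agree on significance in about 68% of trials.

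**Conclusion.** The point holds in a limited form. The article plans two between-arm tests of the same 24-week effect for each scale, names neither as the result, and names no baseline-adjusted analysis for these scales although baseline is collected. The chance of at least one false positive from the pair is about 9% per scale across ρ = 0.3 to 0.7. A single adjusted comparison would be more precise than either test, with a power gain over the better one of about 2 to 10 points for a 0.5 SD effect at 64 per arm.

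These sizes rest on the assumed ρ, equal SDs, the illustrative effect and a baseline unaffected by allocation. The calculation is for the scale scores; the same sentence also covers seizure frequency, to which these formulas do not carry over directly. The primary outcomes are untouched, and nothing here asks for error control across different scales. The change should be made because it is cheap and settles in advance what counts as the answer for each scale.

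**What to change.** In Secondary/additional outcomes, name one 24-week result for each score: PHQ-9, each of the two SF-36 component summaries, and QOLIE-31. It should be the between-arm difference with a 95% CI from a linear model adjusted for that score's baseline, or from a repeated-measures model that also includes 13 weeks. Give a rank-based or bootstrap version if the score is skewed. Report raw means, medians and changes descriptively, and bring the change-over-time sentence in Data analysis into line.

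Because baseline follows randomization:

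- state this where the model is described;
- keep a descriptive comparison of baseline by arm;
- use a pre-randomization screening score as the covariate where one exists;
- report the unadjusted 24-week difference as a sensitivity analysis.

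The cost is wording only, with no new data, visits or participants. The small downsides are that missing baseline scores need a stated handling rule, and that allocation may have influenced the baseline self-report, which the sensitivity analysis is there to show.

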### Process measures

Curran and colleagues define process evaluation as a rigorous assessment approach designed to identify potential and actual influences on the conduct and quality of future implementation and dissemination [33]. The process evaluation will target 2 main areas: (1) Identify and describe program adopter’s perception of the SMART program and (2) “Reach” among clinicians and community partners for SMART referral. Patient perceptions will be assessed via a set of open-ended questions regarding their satisfaction with the program, comprising Likert-style questions assessing positive/negative/neutral components of the program and whether they would recommend participation in SMART to a family member or friend with epilepsy. Referral sources (clinicians, community partners, and other referral sources) will be tracked for all study screens as well as successful enrollments.

### Data analysis

Descriptive analyses will compare the individuals assigned to SMART or WL using Student’s *T*-test, Fisher’s exact test, and non-parametric tests when appropriate. The primary outcome is whether there is a difference in the proportion of individuals with reductions in the total number of NHEs in the prior 6 months, at baseline, and at follow-up (6 months after randomization) between SMART and WL, compared using a Fisher’s exact test. We will also test for the difference in NHE counts between baseline and follow-up using a non-parametric Wilcoxon-Mann-Whitney test (the distribution of this measure is expected to be non-normal based on our prior experience). Exploratory longitudinal mixed models with a subject-level random effect will be conducted to investigate a binary variable of no NHEs versus at least one NHE and for a count measure of total NHEs from baseline to 10 and 24 weeks. Explanatory variables will include study site, age, gender, race/ethnicity, number of seizure medications, rural/urban continuum status, and attendance or deviations from the study protocol. Analysis will be performed for the intention-to-treat population (all participants enrolled to receive the SMART trial), for the safety population (all participants who received any portion of the SMART intervention), and for the per-protocol population (all participants who completed the SMART intervention). There will be a delay between randomization and baseline assessments for individuals enrolled for both the SMART trial and the waitlist, which may vary based on the recruitment time required for cohorts and the number of cohorts that can be accommodated at one time. Every effort will be made to insure steady recruitment and sufficient numbers of cohorts to accommodate those recruited. In addition, the specific cohorts will be able to be identified for analysis, and if we find marked variability between the cohorts or the delay in starting the intervention, this will be addressed by the data monitoring committee.

The 12-month and 18-month measurements of NHEs will be compared to baseline and 6-month measurements as well. We will also examine change-over-time in the secondary outcomes using parametric and/or non-parametric tests as deemed appropriate for each measure. NHE measurements will reflect the preceding 6-month time period, except for the 13-week time period. The 13-week NHE measurement will reflect the time period following baseline (when individuals participating in SMART will be having their “intensive” group sessions), and it will be used to assess for within-subject differences from baseline to 13-week and 13-week to 6-month time periods. Note that the 13-week to 6-month NHE count will be derived by subtracting the measurement taken at 13 weeks from the one taken at 6 months. This will allow for a greater understanding of the time course for when the expected reductions occur in the SMART group, which we expect to mostly occur after the “intensive” 8 group sessions have ended. A secondary analysis of NHEs will include a comparison of hospital and emergency department visits. A 2-sided type I error rate of 5% will be considered significant.

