### Community Advisory Board (CAB)

Building upon strong existing partnerships between members of the study team and epilepsy/neurological care partners across the states of Iowa and Ohio, the study team will obtain input from relevant community stakeholders to develop an a priori recruitment and retention strategy intended to maximize enrollment of typically hard-to-reach individuals with epilepsy from underserved and rural communities. The CAB will be composed of up to 16 individuals, including individuals with epilepsy, epilepsy specialists, clinicians, and administrators who practice in rural or underserved communities, and representatives from the Epilepsy Association/Epilepsy Foundation.

There will be 3 video-conference calls prior to the RCT. In the first call, CAB members will review the SMART curriculum and identify potential barriers to recruitment and retention. In the second meeting, CAB members will review the list of barriers and suggest solutions and strategies for reaching people with epilepsy who may not be initially help-seeking and discuss potential methods of retaining these individuals in the program once they are recruited. In the third CAB meeting, the list of strategies will be finalized, and the investigators will obtain input on how these strategies might be best operationalized.

### Phase 2

Phase 2 is a prospective 6-month comparative trial of SMART vs. WL in 160 individuals with epilepsy and a recent NHE. Participants will be randomly assigned (1:1 basis) to receive either SMART (*N* = 80) or WL (*N* = 80) using a computer-generated random number generator created in REDCap during the enrollment process. This is a simple randomization scheme together with permuted block randomization to insure similar treatment and waitlist group sizes. This randomization scheme is unavailable to study staff who enroll participants and assign to treatment or waitlist groups. The participants and nurse and peer educators are not blinded, due to the nature of the intervention. However, the data analysts have no interaction with participants or the nurse or peer educators. The investigators will conduct 8–10 separate and sequential SMART groups with up to 10 individuals in each group. SMART will consist of two main components: a 12-week remotely accessed “intensive” group format stage and a 12-week remotely accessed Web/telephone follow-up stage.

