#### Primary outcome

The primary outcome will be the proportion of individuals with reduction in their total number of NHEs in the prior 6 months at baseline compared to week 24 of the trial. The prior SMART study had a nonstandard distribution of NHEs and a high proportion of subjects with no NHEs at 6-month follow-up, so a longitudinal binary mixed model (no NHE or at least one NHE) will be used as opposed to a count regression model [10]. The second primary outcome will be the change in NHE counts in the 6 months prior to baseline compared to week 24 of the trial. NHEs are defined as seizures, emergency department visits, hospitalizations, and self-harm attempts. NHE reporting will be via self-report with corroboration by EHR documentation and report of family/support system informants whenever possible. In addition to total NHEs, we will assess NHEs in each category, including seizure frequency and length of stay in days for hospitalization NHEs. These domains (total number of NHEs, seizure frequency, length of hospital stay) will be assessed for differences between the two groups looking at mean and median values. A type I error rate of 0.05 will be considered significant.

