### Sample size calculations

Psychosocial interventions can reduce seizures and emergency department visits in people with poorly controlled epilepsy [34, 35]. Oosterhuis noted a 50% reduction in seizures with group psychoeducation [36]. In our original SMART efficacy trial, a total number of past 6-month NHEs were reduced by > 50%. The projected sample size is 160, with 80 subjects per arm. While the Web and phone-based access format of SMART optimized study retention and attrition rate in the original RCT was 14.2%, we conservatively assume 20% attrition at 6 months (*N* = 128). A 2-sided, 2-sample, Fisher’s exact test with a type I error of 5% will have 86% power to replicate the difference in the proportion of individuals with NHE reductions. For the second primary outcome which has a Laplace distribution, a 2-sided, 2-sample, Wilcoxon-Mann-Whitney test with a type I error of 5% will have 89% power to replicate the difference in NHE counts in the prior 6 months.

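### Fisher's exact test for the first primary outcome is valid but conservative; Boschloo's exact test would give a modest power gain (about 1 to 3 points) without extra participants

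*Protocol article*

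**What the plan says.** The Data analysis section of the protocol article takes the proportion of participants whose total number of negative health events (NHEs) falls as the primary outcome, to be tested "between SMART and WL, compared using a Fisher’s exact test". The level is given in the same section ("A 2-sided type I error rate of 5% will be considered significant") and under Primary outcome ("A type I error rate of 0.05 will be considered significant"). The Sample size calculations section uses the same test and level: "A 2-sided, 2-sample, Fisher’s exact test with a type I error of 5% will have 86% power to replicate the difference". It rests on "The projected sample size is 160, with 80 subjects per arm" and on the statement that "we conservatively assume 20% attrition at 6 months", leaving 128 completers. Allocation is 1:1, as stated under Phase 2. The article does not give the proportion assumed in either arm, and it says nothing about the attained size of the test.

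The Primary outcome section also mentions a binary mixed model. The Data analysis section labels its mixed models exploratory, so I take Fisher's test as the confirmatory one.

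**The concern.** Fisher's test conditions on both margins of the 2×2 table. The design fixes the number randomised per arm but not the total number of participants who improve, so the second condition is not forced by the trial. With about 64 per arm the conditional p-value takes few distinct values near 0.05, and the test rejects a true null noticeably less often than the nominal level allows. That unused error is unused power.

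Boschloo's test takes the Fisher p-value as its statistic and calibrates it over the unknown common proportion. It is also exact, and its rejection region contains Fisher's. In a replication trial of fixed size, a borderline difference that an exact 5% test would call significant could therefore be reported as non-significant.

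**Working it through.** **Inputs from the article.** 80 per arm; 20% attrition; two-sided 5%; Fisher's exact test; stated power 86%.

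**The plan's own figures.** Completers: 160 × 0.80 = 128, as stated, or 64 per arm if losses are equal. The 86% cannot be reproduced because no proportions are given. As an assumption, I take control proportions of 30% to 60% and solve for the SMART proportion at which Fisher's test has 86% power at 64 versus 64.

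**Method.** For arms of n1 and n2 completers and a rejection region R (the set of tables with p at or below a cut-off), the probability of rejection is

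Σ over (x, y) in R of Bin(x; n1, p1) × Bin(y; n2, p2).

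Setting p1 = p2 = p gives the size. Fisher's region uses the cut-off 0.05 on the two-sided Fisher p-value. Boschloo's region uses the largest Fisher p-value cut-off whose size, maximised over p on a 999-point grid, is at most 0.05.

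**Size.**

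| Completers | Fisher size, p = 0.2–0.8 | Boschloo cut-off on Fisher p | Boschloo maximum size |
|---|---|---|---|
| 64 v 64 | 2.97–3.54% | 0.0685 | 4.81% |
| 63 v 65 | 3.57–4.19% | 0.0546 | 4.84% |
| 62 v 66 | 3.51–4.26% | 0.0541 | 4.90% |
| 60 v 68 | 3.46–4.27% | 0.0536 | 4.85% |

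At 64 v 64 Fisher's maximum over all p is 3.54%. In every split checked, Boschloo's region contained Fisher's.

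**Power at 64 v 64.**

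| Control v SMART | Fisher | Boschloo | Gain (points) |
|---|---|---|---|
| 30% v 57.8% | 86.0% | 88.2% | 2.2 |
| 40% v 68.1% | 86.0% | 88.6% | 2.6 |
| 50% v 76.8% | 86.0% | 89.0% | 3.0 |
| 60% v 85.0% | 86.0% | 89.0% | 3.0 |

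**Unequal completer numbers.** For the same pairs at 63 v 65, 62 v 66 and 60 v 68, with the smaller arm as control, the gain runs from about 0.3 to 2.4 points. It is smallest at the 50% control rate.

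Next, let completers in each arm be independent Binomial(80, 0.8), averaged over 56 to 72 per arm (96.7% of the probability). Fisher's size then averages 3.8–4.1%. Over the four pairs its power averages 87.4–87.9% and Boschloo's 88.6–89.3%, a gain of 1.2–1.4 points. Under this model the two arms have equal completer numbers with probability about 8%, and exactly 64 each with probability about 1%.

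**What it can change.** At 64 v 64, 49 versus 38 participants with a reduction gives Fisher p = 0.058 and Boschloo p = 0.042; 47 versus 36 gives 0.064 and 0.044. These are equal-arm cases. At the three unequal splits tabulated the Boschloo cut-off is about 0.054, so a Fisher p of 0.058 or 0.064 would be non-significant under both tests.

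**The case against.** The strongest reply is that nothing here is wrong. Fisher's test is a standard prespecified choice, and the test and level agree between the analysis and sample size sections. That stands. Three further objections deserve an answer.

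- **The level.** A reader might infer that the stated 5% is untrue because the attained size is lower. The article does not support this. A significance level is an upper bound, Fisher's test respects it, and no attained size is claimed.
- **The power.** A reader might infer that the trial falls short of its planned power. It is not shown to. The 86% is quoted for Fisher's test, so an exact calculation already contains the conservatism.
- **No cost at all.** Boschloo's guarantee assumes independent binomial outcomes, and SMART is delivered in groups of up to 10. As an illustration, assume 8 groups of 8 in the SMART arm, a common rate of 40% and an intraclass correlation of 0.02: Boschloo's size is about 5.3% and Fisher's 4.2%. At 0.05 they are 6.5% and 5.2%. These correlations are assumptions, not figures from the article. The slack in Fisher's test does give some incidental protection. But both tests make the same independence assumption, and at the larger correlation Fisher's also exceeds 5%. Clustering is better handled directly than through accidental conservatism.

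The equal-arm figures (size 3.0–3.5%, gain 2–3 points) must also not be read as the expected case, because exactly equal completer numbers are unlikely.

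**Conclusion.** The point holds as an optional efficiency gain of modest size. Fisher's test at a nominal two-sided 5% attains about 3.0–3.5% at exactly 64 versus 64, and about 3.5–4.3% at mildly unequal splits, for common proportions between 0.2 and 0.8. Replacing it with Boschloo's test adds about 2–3 points of power at 64 versus 64, and a little over 1 point on average under random attrition. The gain was never negative in any split checked.

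The size figures need only the article's numbers and a range of common proportions. The power figures also depend on assumed control rates of 30–60%, on SMART rates solved to give 86%, on independent 20% losses per arm for the average, and on independent outcomes. The exact gain for this trial cannot be fixed without the sponsor's proportions.

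**What to change.** In the Data analysis section, name Boschloo's exact unconditional test at two-sided 0.05 for the first primary outcome in place of Fisher's, and report the risk difference with an exact unconditional confidence interval. Fisher's test can stay for the descriptive comparisons.

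In the Sample size calculations section, state the two proportions assumed and recompute the power for the new test from them. Describe the result as a modest gain over 86%; a fixed 88–89% would hold only for exactly equal completer arms. Add a sentence acknowledging that the exact guarantee assumes independent outcomes, given group delivery of SMART.

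The cost is a few sentences and one recalculated figure, using standard software (R or Python), with no new data, visits or participants. The change should be made before outcome data are seen, since a later switch to a more powerful test would not be credible. If the sponsor prefers to keep Fisher's test, the analysis remains valid.

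### Both primary tests are valid but ignore the baseline NHE count, and so give up power that baseline adjustment would recover without extra data

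*Protocol article*

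**What the plan says.** The Protocol article fixes both primary comparisons as two-sample tests. Under Data analysis, the proportion with fewer NHEs is examined "between SMART and WL, compared using a Fisher’s exact test", and for the counts: "We will also test for the difference in NHE counts between baseline and follow-up using a non-parametric Wilcoxon-Mann-Whitney test". The Primary outcome section gives the second endpoint primary status: "The second primary outcome will be the change in NHE counts in the 6 months prior to baseline compared to week 24".

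Sample size calculations powers the trial on the same two tests. For the responder outcome: "A 2-sided, 2-sample, Fisher’s exact test with a type I error of 5% will have 86% power". For the count outcome: "Wilcoxon-Mann-Whitney test with a type I error of 5% will have 89% power to replicate the difference in NHE counts". It also states: "The projected sample size is 160, with 80 subjects per arm", of whom 128 (64 per arm) are expected to be evaluable after 20% attrition.

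An NHE in the preceding 6 months is an entry requirement, so each participant has a baseline count. Covariates appear only in mixed models that Data analysis labels exploratory. Their list includes site, age, gender and rurality, but not the baseline NHE count.

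**The concern.** A participant with 1 prior event and one with 50 have very different chances of showing any reduction and very different possible changes. The unadjusted tests leave that variation in the noise, and chance imbalance in baseline counts carries into the change. Fisher's exact test is also conservative at this sample size. The plan itself expects a skewed count distribution, which is where a few high counters matter most. What is at stake is power on both primary outcomes in a sample of 128. Bias and type I error are not at stake.

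The binary mixed model named under Primary outcome does not fill the gap. Data analysis calls it exploratory. Its outcome, no NHE against at least one, is also nearly constant at baseline because entry requires a recent NHE, so it carries little of the baseline count.

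**Working it through.** **1. The plan's own figures.** Evaluable sample: 160 × (1 − 0.20) = 128, which agrees. The stated powers of 86% and 89% cannot be reproduced, because no per-arm proportions and no shift or scale are given. Working backwards at 64 per arm:
- Fisher reaches 86% at, for example, 40% vs 68%, 50% vs 77% or 60% vs 85%. At such proportions an uncorrected chi-square test has about 89 to 90%. Fisher's conservatism alone therefore costs 3 to 4 points.
- For the count outcome the plan says only this about its shape: "For the second primary outcome which has a Laplace distribution". Wilcoxon-Mann-Whitney power of 89% then needs a shift of about 0.48 SD.

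**2. Normal-theory benchmark for the count outcome.** Let ρ be the baseline to follow-up correlation (assumed; not in the documents). The variance of the change is proportional to 2(1 − ρ) and the baseline-adjusted variance to 1 − ρ². Their ratio is (1 + ρ)/2. Anchored at 89%, adjusted power = Φ[(1.960 + 1.227) × √(2/(1 + ρ)) − 1.960].

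| ρ | Variance ratio | Adjusted power | Evaluable N giving 89% (128 × ratio) |
|---|---|---|---|
| 0.3 | 0.65 | 97.7% | 83 |
| 0.5 | 0.75 | 95.7% | 96 |
| 0.7 | 0.85 | 93.3% | 109 |
| 0.9 | 0.95 | 90.5% | 122 |

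The gain runs from 1.5 points (ρ = 0.9) to 8.7 points (ρ = 0.3).

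**3. Simulation with skewed counts.** Assumptions: gamma-Poisson counts, baseline at least 1, rate ratio 0.5, 64 per arm. Settings are written as (between-person shape, mean, within-person shape). With 1,000 runs the standard error is at most √(0.25/1000) = 1.6 points.

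| Setting | Wilcoxon on change | Ranked change adjusted for ranked baseline | Gain |
|---|---|---|---|
| (0.5, 10, 1.5) | 60% | 75% | 15 |
| (0.5, 10, 4) | 90% | 97% | 7 |
| (0.5, 10, 4), a further 30% event-free in both arms | 58% | 77% | 19 |

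Adjusting the ranked change beat plain Wilcoxon in all 11 non-null settings examined, by about 7 to 22 points. Null rejection was 4.6 to 5.3%. In the third setting, ranking the 6-month count in place of the change cut power from 58% to 38%.

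**4. Responder outcome.** Power in one set of runs, splitting the gain into its two parts:

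| Setting | Fisher | Chi-square, unadjusted | Logistic with log baseline | From dropping Fisher | From baseline |
|---|---|---|---|---|---|
| (0.5, 10, 1.5) | 53% | 62% | 65% | 9 | 3 |
| (0.3, 20, 2) | 65% | 71% | 72% | 6 | 1 |
| (1, 5, 2) | 59% | 66% | 70% | 7 | 4 |

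At (0.5, 10, 4) the chi-square and logistic powers were practically equal (84.6% and 84.7%). Across all checks the total gain was about 6 to 14 points, of which baseline itself added roughly 0 to 6. Under the null, Fisher rejected in 2.4 to 3.7% of runs and the logistic test in 4.2 to 5.7%.

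A separate Poisson-lognormal model, with the effect set so that Fisher had 82 to 88% power, gave 93 to 95% for the adjusted logistic test.

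**The case against.** The best defence is that randomisation makes both tests valid, that the stated power is already 86% and 89%, and that a replication trial has reason to repeat the original trial's analysis. Four points add to it.

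- **Distribution.** The Primary outcome section reports many participants with no NHEs at follow-up in the prior study, and an adjusted test on the ranked 6-month count can lose power in that case. This stands against ranking the 6-month count. It does not stand against ranking the change, which kept its advantage with 30% extra zeros.
- **Source of the responder gain.** Most of it comes from replacing Fisher, not from the covariate. This stands, and the size is stated accordingly.
- **Calibration.** Several settings put the planned tests well below 86% and 89%. This stands in part. In the setting that matches the stated Wilcoxon power, the count gain is 7 points, the low end of the range.
- **Timing.** Data analysis allows a delay between randomisation and the baseline assessment. Participants are unblinded and NHEs are self-reported, so the baseline value may not be a pre-randomisation one. This stands and shapes the fix.

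A reader might also infer that PHQ-9, SF-36 and QOLIE-31 are committed to unadjusted tests of change. The text does not say so: "We will also examine change-over-time in the secondary outcomes using parametric and/or non-parametric tests as deemed appropriate for each measure". That wording leaves the method open and does not exclude ANCOVA, so the secondary scales form no part of this point.

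**Conclusion.** The point holds as a loss of efficiency in both primary analyses, and it should be changed. Under assumed count distributions at 64 per arm, the count test stands to gain about 7 to 22 percentage points. The responder test stands to gain about 6 to 14 points over Fisher, most of it from removing Fisher's conservatism. Size stays near 5%. The normal-theory benchmark shows a gain at every correlation tried, but a small one when correlation is high.

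Two stronger readings are not supported. The planned tests are not invalid or biased. Nor do the documents show that the trial is underpowered: they give no effect size, correlation or distribution from which to recompute the stated power, and the lower simulated powers reflect the assumed settings. For the same reason, the exact gain in this trial is unknown.

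**What to change.** - **Count outcome.** Keep the change in NHEs as the endpoint. Regress ranks of the change on arm, ranks of the baseline count and site, in place of plain Wilcoxon-Mann-Whitney. Do not substitute ranks of the 6-month count. The method stays rank-based, so it respects the plan's reservation about count regression.
- **Responder outcome.** Use logistic regression of reduction on arm, log baseline count and site. Report a standardised risk difference, so that the result stays on the scale of proportions and is not a conditional odds ratio.
- **Sensitivity analyses.** Keep Wilcoxon-Mann-Whitney and Fisher's exact test for comparison with the original trial.
- **Covariate definition.** Use the NHE count for the period before randomisation, for example from screening, where available.

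The cost is a change of wording, to be prespecified before any comparison by arm. The variables are already collected, subject to the availability of a pre-randomisation count. The downside is that the results are slightly less simple to describe.
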